[figure not shown]

## PROJECT DESCRIPTION

### *Background and rationale of the study*

Over the last decade, personalized medicine (PM) has undergone considerable development, sparking a veritable revolution in healthcare [1]. By combining genetic information, environmental and behavioral characteristics, and the specific socioeconomic and cultural context of each individual, the aim is to identify the best treatment, tailored to their unique characteristics [2,3].

In this context, Personalized Prevention has been developed, with the aim of identifying the best approaches to prevent the onset and promote early diagnosis of major diseases. A change in strategy, moving away from a system based on treating individuals, is necessary in light of the aging of the general population and the increase in age-related diseases [1,4]. The National Recovery and Resilience Plan (PNRR), approved in 2021 as part of the European Next Generation EU program, has two objectives for the national healthcare system: on the one hand, to modernize the country, especially by promoting digital healthcare and technological development, and on the other, to promote strategies for early diagnosis and disease prevention [5,6].

Cardiovascular disease (CVD) is the leading cause of mortality and morbidity in Europe and is due to a combination of unhealthy lifestyles, environmental factors, and genetic predisposition [7]. There are numerous genetic variants associated with the onset of cardiovascular disease, and their impact can be measured using the Polygenic Risk Score (PRS), which estimates each individual's predisposition to developing the disease by weighting the influence of each individual variant. These scores can be used to implement personalized preventive strategies, tailored to each patient's risk profile, to delay or prevent the onset of disease [8,9,10,11,12].

Over the last two decades, the prevalence of risk factors for cardiovascular disease has increased significantly. Unhealthy diets, physical inactivity, and cigarette smoking are particularly high among young people aged 18-35, predisposing them to the development of cardiovascular disease [13], with dramatic consequences for the future of the national health system. The latest data predict a 20% increase in mortality by 2030 compared to 2019 data, and an increase in DALYs (Disability Adjusted Life Years) [14].

In light of this epidemic of cardiovascular disease, prevention becomes a fundamental objective for global healthcare systems. It is well known that improving one's eating habits, increasing physical activity, and quitting smoking reduce the risk of developing cardiovascular disease and, consequently, lead to a decreased burden in older age groups. [15,16]

The aim of this study is to encourage a healthy lifestyle in healthy individuals with low traditional cardiovascular risk by communicating their genetic predisposition risk profile, measured by calculating their PRS. This study would allow for the evaluation of innovative personalized approaches, with the ultimate goal of reducing the burden of future cardiovascular disease and the associated costs.

## **OBJECTIVES**

### ***General objective***

The general objective of the study is to evaluate changes in lifestyle after communicating the Polygenic Risk Score, measured using a validated questionnaire.

### ***Primary objective***

- To evaluate the effectiveness of communicating the Polygenic Risk Score in modifying participants' lifestyle.

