## **ENDPOINTS**

### ***Primary endpoint***

- Pre-post change in lifestyle score, measured using Life Essentials' 8, at baseline and at final follow-up [17,18,19,20]
- Changes in cardiovascular risk profile assessed using SCORE2 / SCORE2 OP

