## **METHODS**

### ***Study design***

Single-center, single-arm experimental study conducted on a cohort of subjects attending the A. Gemelli IRCCS University Hospital in Rome (Italy), enrolled at the outpatient clinics of the Cardiology Department.

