During the informative telematic visit (T1), the lifestyle score will be explained. Participants will receive personalized written preventive advice to reduce unhealthy behaviors and modify their lifestyle. The PRS results will also be disclosed to all participants and the risk profile category will be provided, with all relevant information. At the six-month follow-up from T1 (T2), participants will receive a complete final assessment, as at T0, which includes the submission of the lifestyle questionnaire and the recalculation of the lifestyle category, as well as biometric tests (weight, BMI, body circumferences, heart rate, blood pressure). At the same time, for a new SCORE2/SCORE2 OP assignment, a blood sample will be taken for the re-evaluation of the lipid profile (total cholesterol, HDL, LDL), blood glucose/glycated hemoglobin. In addition, lipoprotein (a) and troponin I will be measured.

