### **Statistical Analysis**

The statistical analysis involves the application of descriptive statistics to describe the sample analyzed in terms of personal data, lifestyles, health factors, blood chemistry parameters collected at baseline, and attitudes. Changes in lifestyle will be analyzed using adjusted mixed-effects models for repeated measures. A potential list of moderators and mediators of the relationship between intervention and behavioral change (such as sociodemographic characteristics, ethnicity, socioeconomic status, education, PRS levels) will be analyzed to evaluate the mechanisms that explain why the intervention may or may not lead to change, i.e., whether people with certain characteristics may benefit more or less from it. Statistical analyses will be conducted using STATA (StataCorp, USA) and R.

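### The primary objective credits lifestyle change to PRS communication, but in a single arm that also gives everyone lifestyle feedback and advice, the pre-post change cannot show this

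*Protocol*

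**What the plan says.** The primary objective (Protocol, Primary objective) is "To evaluate the effectiveness of communicating the Polygenic Risk Score in modifying" lifestyle. The design (Study design) is a "Single-center, single-arm experimental study conducted on a cohort of subjects", with no comparator.

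The Procedures section describes three things that happen at T1, about one month after enrolment:

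- Each person's lifestyle score is explained to them.
- Tailored advice is handed over in writing: "Participants will receive personalized written preventive advice to reduce unhealthy behaviors and modify their lifestyle".
- Genetic results are given at this same visit, with nobody exempted: "The PRS results will also be disclosed to all participants and the risk profile category will be provided".

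The first primary endpoint is "Pre-post change in lifestyle score, measured using Life Essentials' 8, at baseline and at final follow-up". The Questionnaire section places LE8 at T0 and T2 only. T2 is six months after T1.

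The Statistical Analysis section plans adjusted mixed models for repeated measures. It also plans to examine "A potential list of moderators and mediators of the relationship between intervention and behavioral change", giving sociodemographic characteristics, ethnicity, socioeconomic status, education and PRS level as examples, in order to learn who may gain more or less from the intervention.

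The General objective is worded differently. It asks only how lifestyle changes after the PRS has been communicated.

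**The concern.** The primary objective is causal and names one component. The design delivers that component together with two others, one of which (the written advice) is aimed directly at the primary outcome. Nobody goes without the PRS, the three components are not staggered, and LE8 is not measured between them.

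Other influences enter the same T0-T2 change. There is a full medical examination at T0. Participants are recruited through cardiovascular prevention clinics, so other care is plausible. Baseline and follow-up fall in different seasons. The T0 blood values may be up to six months old, whereas the T2 sample is fresh.

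What is at stake is the headline conclusion. Under the objective as worded, a significant rise in LE8 would answer a question about PRS communication, although advice alone could have produced it. The same difficulty affects the claim about who benefits more: when everyone is exposed, a baseline variable can predict change, but that does not show that it modifies the effect of the intervention.

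**Working it through.** **1. The plan's own figures.** From Sample calculation: 650 × 0.70 = 455 enrolled, and 455 × 0.80 = 364 completers. The target is a mean LE8 change of 3 points with SD 2, read here as the SD of the change. The protocol gives no alpha, so two-sided 5% is assumed. With √364 = 19.08, the standardised change is 3 × 19.08 / 2 = 28.6, and power is effectively 100%. The stated power above 90% is reproduced. It is power to detect a non-zero change of any origin.

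**2. What the change contains.** Write the mean T0-T2 change, taking effects as additive for simplicity, as

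Δ = p + a + f + b,

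where p is PRS disclosure, a the advice, f the lifestyle-score feedback and b all background change. One arm measured twice estimates Δ and nothing else. A change of Δ = 3 fits p = 0 with the rest 3, p = 3 with the rest 0, p = 4 with the rest −1, or p = −1 with the rest 4. A larger sample narrows the interval for Δ but does not inform p.

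**3. Chance of a significant result when p = 0.** Let a + f + b = d. Power ≈ Φ(d × 19.08 / SD − 1.96). SD 2 is the protocol's; SD 5 and 10 are assumptions that show the range.

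| d (points) | SD 2 | SD 5 | SD 10 |
|---|---|---|---|
| 1.0 | Φ(7.58) ≈ 100% | Φ(1.86) ≈ 97% | Φ(−0.05) ≈ 48% |
| 0.5 | Φ(2.81) ≈ 99.7% | Φ(−0.05) ≈ 48% | Φ(−1.01) ≈ 16% |

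A small effect of advice or time is thus enough to make the primary analysis positive with no PRS effect, most readily at the protocol's own SD.

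**4. What the PRS-level contrast estimates.** Suppose feedback, advice and background act equally in all PRS categories and sum to c. The mean change is p_H + c in the high category and p_L + c in the rest, so the difference is p_H − p_L. The effect of communicating the PRS across the cohort is instead a weighted average of p_H and p_L. Two illustrations, assuming 20% are in the high category:

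- p_H = p_L = 3: the contrast is 0, although communication adds 3 points for everyone.
- p_H = 2, p_L = −0.5: the contrast is 2.5, although the cohort effect is 0.2 × 2 − 0.8 × 0.5 = 0.

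The contrast is therefore informative about the result received, not about disclosure versus none.

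**5. Its precision.** With 20% of 364 in the high category (73 versus 291, assumed), SE = SD × √(1/73 + 1/291) = SD × 0.131. This gives 0.26 at SD 2, and 1.05, 1.31 and 1.57 at assumed SDs of 8, 10 and 12, before any gain from baseline adjustment.

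**The case against.** The single-arm design is openly declared, and such designs are legitimate. The general objective and the primary endpoint are descriptive, and the protocol contains no rule that a positive result be reported as a PRS effect. All of this stands. The fault lies in the wording of the primary objective, which claims more than the rest of the protocol can deliver. An unseen SAP cannot cure that, because the data will contain no participant without disclosure.

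Several stronger readings are tempting, and the document does not support them:

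- **That PRS category by time rescues the objective.** It compares higher with lower results. It also removes the other influences only if these act equally across categories. The protocol does not say that the advice is independent of PRS category. LE8 includes cholesterol and blood pressure, and entry is restricted on SCORE2/SCORE2-OP, so equality is not assured.
- **That mediation is impossible and the term must go.** The variables named all precede T1, so those examples cannot mediate. But the list is open, and the protocol collects post-disclosure measures (FACToR at T2, GAD-7 at T0 and T2). Mediation would be weakly identified without a control; it is not excluded by the text.
- **That the PRS share lies between 0 and 100%.** This is not a bound. If background change is negative or a result reassures, the share can exceed 100% or fall below zero.
- **That regression to the mean inflates the change.** Entry does not select on poor LE8 and excludes very high risk, so its direction is not established.
- **That 3 points is the right yardstick for a between-category difference.** In the protocol it is the total pre-post change.

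**Conclusion.** The point holds for the primary objective and the conclusion drawn from it. The study can estimate LE8 change after a combined package; it cannot attribute that change, in whole or part, to communicating the PRS. This follows from the single arm, the joint delivery at T1 and the two measurement times, and depends on no assumed number. The probabilities in the table illustrate the consequence. They rest on 364 completers, a two-sided 5% test and, apart from SD 2, assumed SDs.

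A reader might infer that the study is invalid or must be randomised. Neither follows: the general objective is answerable as the study stands. The primary objective should be corrected because it governs the headline claim. The planned PRS-level analysis is worth keeping as supportive evidence.

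**What to change.** 1. Reword the primary objective and planned conclusion as *change in LE8 after a combined package of PRS disclosure, lifestyle-score feedback and personalised advice*, with no attribution to the PRS alone. This brings them into line with the descriptive general objective.
2. Pre-specify LE8 change by PRS category, adjusted for baseline LE8, as a supportive analysis. State that it estimates the effect of receiving a higher rather than a lower result, not of disclosure versus none, and that it is interpretable only if the advice does not vary by PRS category.
3. In Statistical Analysis, describe sociodemographic and similar baseline variables as exploratory predictors of change, not as evidence of who benefits more from the intervention.

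The cost is protocol wording, one pre-specified analysis and a more modest headline claim, with no extra participants or visits.

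A causal PRS claim would need a concurrent group given the same advice, with disclosure delayed until after T2. That is a redesign outside this fix, and it is not free. If the 364 completers were split 182 to 182 with an assumed SD of 10, power would be about 82% if the PRS added the full 3 points and about 30% if it added 1.5. The delayed group also could not report reactions to its result at T2, when FACToR and the acceptability questionnaire are collected.

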### ***Secondary objective***

- Assess the feasibility of introducing the Polygenic Risk Score into the patient care pathway

## **ENDPOINTS**

### ***Primary endpoint***

- Pre-post change in lifestyle score, measured using Life Essentials' 8, at baseline and at final follow-up [17,18,19,20]
- Changes in cardiovascular risk profile assessed using SCORE2 / SCORE2 OP

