### ***Inclusion criteria***

- Traditional cardiovascular risk, measured using SCORE 2 (Low risk (< 2.5%); Moderate risk (between 2.5% and 5%); High risk (between 5% and 10%) or with SCORE 2-OP (Moderate risk (< 7.5%); High risk (between 7.5% and 15%))
- Availability of blood tests within the previous 6 months
- Subjects aged  $\geq 40$  years.

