### ***Exclusion criteria***

- Very high cardiovascular risk measured using SCORE 2 (very high risk > 10%) or SCORE 2-OP (very high risk > 15%)
- Diabetes
- Familial hypercholesterolemia
- Previous cardiovascular events

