## **STATISTICAL ANALYSIS**

### **Sample calculation**

The study will be offered to all employees of the Policlinico Gemelli hospital who meet the inclusion criteria listed above ( ). It is estimated that out of a total of approximately 650 subjects who will be offered the intervention, 70% will participate in the project (N=455) and of these, 80% will complete the study (N=364). This sample size allows us to detect a mean difference of LE8 equal to 3 points (standard deviation=2) between the end and the beginning of the follow-up with a power greater than 90%.

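### SCORE2/SCORE2-OP change is listed as a second primary endpoint outside the objective and the sample size, and nothing stops participants' ageing between visits from moving it

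*Protocol*

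**What the plan says.** The Primary endpoint section of the protocol has two entries: "Pre-post change in lifestyle score, measured using Life Essentials' 8, at baseline and at final follow-up" and "Changes in cardiovascular risk profile assessed using SCORE2 / SCORE2 OP". The second entry does not say whether the change is in a percentage or in a category.

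The Primary objective is narrower: "To evaluate the effectiveness of communicating the Polygenic Risk Score in modifying participants' lifestyle". The Sample calculation expects 364 completers and says that this number can "detect a mean difference of LE8 equal to 3 points", with an SD of 2 and power above 90%. It gives no target, SD or power for SCORE2/SCORE2-OP.

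Under Procedures, results are communicated about one month after T0 (visit T1), and T2 follows six months after that. At T2, "for a new SCORE2/SCORE2 OP assignment, a blood sample will be taken". No sentence says which age, or which of the two instruments, is used in the T2 calculation. The Inclusion criteria admit anyone aged 40 or over with no upper limit, and use both instruments with different category limits. The Study design is single-arm.

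**The concern.** A primary endpoint should respond to what the trial is trying to change. A cardiovascular risk score that includes age also responds to the calendar. Participants are about 7 months older at T2, so a person whose habits, blood pressure and lipids are exactly as before would score slightly higher. In a randomised comparison this would cancel between arms. In a pre-post comparison with one arm it becomes part of the estimate.

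The bias runs against the intervention. A modest real improvement could be cancelled, or no effect could appear as statistically significant worsening, in a result that the protocol labels primary. Nothing else in the protocol supports that label, since neither the objective nor the sizing refers to the risk score.

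**Working it through.** **1. The plan's own figures.** 650 × 0.70 = 455 participants; 455 × 0.80 = 364 completers. Taking the stated LE8 difference of 3 and SD of 2 as a paired change, with two-sided alpha 0.05 (assumed, as none is stated), power = Φ(3 × √364 / 2 − 1.96) = Φ(28.6 − 1.96), which exceeds 0.999. The claim of more than 90% is correct on its inputs, but it concerns LE8 only. For SCORE2, all that can be said is that N = 364 detects a standardised change of (1.96 + 1.28)/√364 = 0.17 with 90% power. Without an SD or a target, that cannot be turned into risk points.

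**2. Age drift.** Interval T0 to T2: 1 + 6 = 7 months. Assumptions not in the documents: age is an input to the score, and predicted risk rises by a relative 3-10% per year of age.

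- Relative drift = (1 + r)^(7/12) − 1. For r = 0.03 this is 1.7%; for r = 0.10 it is 5.7%.
- At a 5% risk: 0.087 to 0.286 percentage points.
- At a 2.5% risk: 0.043 to 0.143 percentage points.

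Entering age in whole years changes little on average. About 7 in 12 participants would pass a birthday, giving a mean drift of 7/12 × 3% = 1.75% to 7/12 × 10% = 5.8%.

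**3. Chance of a significant rise when behaviour does not change.** SE = SD/√364, which is 0.052 for an assumed SD of change of 1 point and 0.105 for 2 points. Chance = Φ(drift/SE − 1.96).

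| Baseline risk | SD of change | r = 3% per year | r = 10% per year |
|---|---|---|---|
| 5% | 1 point | 0.38 | > 0.99 |
| 5% | 2 points | 0.13 | 0.78 |
| 2.5% | 1 point | 0.13 | 0.78 |
| 2.5% | 2 points | 0.06 | 0.28 |

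Without drift, each entry would be 0.025.

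**4. Change of instrument.** Under the Inclusion criteria, a risk between 5% and 7.5% is High on SCORE2 and Moderate on SCORE2-OP. A risk below 2.5% is Low on SCORE2 but falls in the Moderate band of SCORE2-OP. A person who changes instrument between visits can therefore change category, in either direction, with the same percentage. The documents do not give the age at which the instrument changes. Assuming one threshold and ages spread evenly over 20 to 50 years around it, the share crossing in 7 months is (7/12)/50 = 1.2% to (7/12)/20 = 2.9%, or about 4 to 11 of 364.

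**The case against.** The strongest reply is that the protocol leaves the T2 calculation open and does not fix it badly. The age and instrument used, the scale of the change and the handling of two primaries could all be settled in a statistical analysis plan that is not shown. That is fair for testing order and alpha, and no finding is made on those. It does not answer the rest. The primary endpoints are set in the protocol, which places the risk score among them while its objective and sizing cover lifestyle alone. It also calls for a new assignment at T2 without holding anything at T0.

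The size of the drift can also be challenged, because the age effect and the SD are both assumed. That stands. At a 2.5% risk, which the inclusion criteria allow, the chance of a significant rise is about 6-78%, well below the upper figures at 5%. The calculation also treats the endpoint as a continuous percentage, which is only one reading of the protocol's wording.

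Stronger readings are tempting, but the documents do not support them:

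- **False success.** A reader might infer that two primaries at 5% give a 9.75% chance of false success (1 − 0.95² = 0.0975). That needs an either-one-suffices rule that the protocol does not state, and it counts significant worsening as success. Counting improvement only, with no drift, the figure is 1 − 0.975² = 4.9%. Upward drift makes a false SCORE2 improvement rarer still: with 0.087 points and SD 2, Φ(−1.96 − 0.83) is about 0.003, against 0.025.
- **Regression to the mean.** A reader might infer that excluding very high T0 scores pushes T2 upward. Recruitment at cardiovascular prevention clinics could select raised readings, which would pull T2 downward. The documents do not fix the sign.
- **Instrument switching as a main source of bias.** It would touch only a few participants, and fewer if the employee sampling frame in the Sample calculation means that few are near the changeover age.

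**Conclusion.** The concern holds in a limited form. SCORE2/SCORE2-OP change is a primary endpoint outside the stated objective and without sizing. As written, its T2 value can include ageing that has nothing to do with behaviour, in a design with no control. If age enters the score, the direction is upward, against the intervention. The risk is a masked benefit or an apparent worsening, not a false claim of benefit.

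The size rests on assumed inputs. A relative drift of about 1.7-5.7% over 7 months would cancel a true relative reduction of the same size. At a 5% risk, the chance of a significant rise under no effect runs from about 13% to over 99%. So wide a range shows that the problem may be material, not how large it is. Category changes from switching instrument are a minor addition. This should be fixed, but it does not touch the LE8 endpoint or its power.

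**What to change.** 1. State that the T2 SCORE2/SCORE2-OP value used for the change is calculated with the T0 age and the T0 instrument, so that only modifiable inputs can move it. Report the score at actual age descriptively.
2. Make LE8 change the sole primary endpoint, in line with the Primary objective and the Sample calculation, and move SCORE2/SCORE2-OP change to the secondary endpoints. State there whether the change is in percentage points or in category.

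The cost is a protocol wording change and a small change to the calculation. SCORE2/SCORE2-OP loses primary status. No new data are needed, and the LE8 sample size stands as written. If the sponsor prefers to keep two primaries, the alternative is to say whether one or both must succeed and to size SCORE2/SCORE2-OP. That needs an SD and a target that the protocol does not have, and step 1 would still be required.
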